### Cost analysis

In order to estimate the financial cost of public involvement in quality-indicator prioritisation, a cost analysis will be conducted. In this type of analysis, the costs of an intervention are presented in a disaggregated form [86]. We will adopt the perspective of the intervention sponsor and report on the marginal financial costs of public involvement, including the costs of public representatives' recruitment, training, financial compensation, group facilitation, administrative support, meals, and didactic material. The average costs per site will be estimated based on actual project expenses.

### Process evaluation

In the context of trials, process evaluation can be used to explain the study's results [87,88]. Our process evaluation will focus on understanding the effects of the intervention and the mechanisms that underlie change. A multiple case study will be used for this analysis, capitalising on natural intersite variations. Our analysis will be guided by group process and deliberative theory to explore how public involvement influences the content of deliberation and the social interactions among participants [39,89-91]. Data collection will be carried out using standardised questionnaires, direct observation of all meetings by two independent nonparticipant observers, and video recording of all meetings. A group debriefing session will be held with participants at the end of each meeting. A standardised self-administered evaluation questionnaire will also be distributed at the end of each meeting, based on an existing deliberation assessment questionnaire [92]. The evaluation questionnaire is composed of 22 items divided into five domains covering (1) roles, procedures, and objectives; (2) meeting facilitation and support; (3) information received; (4) participants' interaction; and (5) overall satisfaction. Each item is scored on a 7-point Likert scale. The observers and moderators will hold a debriefing session among themselves immediately after each meeting to share observations.

### Statistical analysis

Descriptive statistics will be used to summarise the characteristics of the study population and assess the comparability of intervention and control groups, as well as to summarise data on quality-indicator choice, intended use, and on the marginal costs of the intervention.

We will descriptively report which quality indicators are selected as targets for improvement within each site at the end of the trial and calculate the proportion that are in agreement with local public baseline priorities (ranks 1 to 5). Individual quality-indicator priorities will be analysed as a dichotomous measure by reporting the proportion of participants who selected each indicator as part of their five priorities and by calculating its rank (rank 1 = indicator selected by the greatest proportion of participants). Agreement with public priorities will be analysed by calculating the correlation between professionals (clinicians and managers) and public priorities at baseline and at the end of the trial (primary outcome). Cluster randomisation leads to a reduction of effective sample size and can give spurious statistical results if it is not accounted for properly [93,94]. We will check the data to assess the level of clusterisation within study sites and use appropriate cluster-level analysis (*e.g.*, multilevel modelling) if necessary. We will also compare decision makers' intention to use the selected indicators and participants' satisfaction between intervention and control sites. Statistical significance will be assumed at *p *< 0.05 (two-tailed test) for all tests.

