Many doubts remain regarding the feasibility and impact of public involvement in quality improvement [14,42-44]. To date, most empirical research on public involvement in healthcare has studied the process of involvement and its perception by participants (*e.g.*, whether public representatives are satisfied with the experience and feel that deliberations were fair); no study has assessed the impact of public involvement in quality-indicator prioritisation [14]. A recent knowledge synthesis identified many barriers to the development of effective involvement programs, including the following: the lack of evidence on public-involvement effectiveness, concerns that public involvement may often be tokenistic and is unlikely to influence group decision making, the technical complexity of the task, the difficulty in identifying and recruiting public members who are competent and representative, the gap between professional and public perspectives, and the feasibility of public-involvement interventions in terms of time constraints and cost [45].

Our goal is to assess the feasibility and impact of public involvement on quality-indicator prioritisation. Our specific aims are the following:

1. Evaluate the impact of public involvement on:

a. quality-indicator choices and agreement with public priorities (primary outcome);

b. decision makers' intention to use the indicators for quality improvement.

2. Identify factors that explain the effectiveness of the public-involvement program.

3. Estimate the costs of involving the public in quality-indicator prioritisation.

Our main hypothesis is that public involvement will result in quality-indicator choices that better agree with public priorities.

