**Figure 2 F2:**
[figure not shown]
**Systematic review of quality indicators flowchart**. Systematic review and selection of existing validated quality indicators for chronic disease prevention and management in primary care.

We identified a total of 1489 individual indicators. 801 indicators met our inclusion criteria. We extracted each included individual indicator and built a quality-indicator database. Two independent researchers, including the principal investigator, identified and removed duplicates. When multiple related clinical care indicators were present, we chose indicators that were developed in Canada or that were most closely aligned with current Canadian clinical practice guidelines [60-65]. We presented the remaining list of individual indicators to a panel of five experts (two physicians, two health managers, and an information specialist) who shared collective expertise in the clinical and organisational aspects of chronic disease management and knowledge of the clinical context and the available information systems. Expert panel member independently rated each indicator based on relevance and measurability. Expert panel members met twice to agree on the final list of indicators.

Primary care delivery in Canada is largely provided by family physicians, but allied health professionals, such as primary care nurses and nurse practitioners, are playing an increasing role in this area. To reflect these system characteristics, we adapted the wording of some indicators by changing 'regular doctor' to 'family doctor' or 'regular primary healthcare provider', in accordance with current Canadian indicators [66]. We translated the selected indicators in French and wrote a plain language description of each. Our expert panel validated the indicator translation and description. Subscales of individual questionnaires (*e.g.*, the Primary Care Assessment Survey continuity domain [67]) and disease-specific clinical indicators (e.g. clinical management of type 2 diabetes) were grouped together as individual menu items.

The proposed indicator menu was tested for comprehensiveness and relevance with a group of public representatives and professionals in our pilot project (described below). The final menu of indicators is composed of 37 menu items (Table 1). The complete description of each indicator and a reference to the original indicator set is included in Additional file 1.

**Table 1 T1:** Menu of quality indicators

Access	

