### Quality-indicator prioritisation

Our primary outcome is the comparison of indicator choice and agreement with public priorities between intervention and control groups. Data on quality-indicator prioritisation will be collected at baseline and at the end of each meeting (Figure 3). In order to collect public baseline priorities from all participating sites, we will hold step 1 meetings with public representatives from the six participating sites. Clinicians and managers' baseline priorities will be collected at the beginning of the step 2 meeting. Postdeliberation priorities will be collected at the end of the step 2 meeting. Decision makers' choice and final priorities will be collected at the end of the step 3 meeting. We will also collect postconsultation priorities from control site participants at the end of the step 3 meeting, after we collect data on decision makers' choice and intention to use and present results of public consultation. Postdeliberation and postconsultation priorities will be used for process evaluation purposes to assess the contribution of each component of the intervention.

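### The primary hypothesis compares arms, but the stated primary analysis is a within-group correlation, and use of the site as unit is left to a look at the data

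*Protocol article*

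**What the plan says.** The Background gives a directional hypothesis about the intervention: "Our main hypothesis is that public involvement will result in quality-indicator choices that better agree with public priorities". The section Quality-indicator prioritisation says: "Our primary outcome is the comparison of indicator choice and agreement with public priorities between intervention and control groups".

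The Statistical analysis section first reduces each person's five choices to figures per indicator, "by reporting the proportion of participants who selected each indicator as part of their five priorities and by calculating its rank". It then states: "Agreement with public priorities will be analysed by calculating the correlation between professionals (clinicians and managers) and public priorities at baseline". The sentence adds the end of the trial as a second time point and carries the primary-outcome label. No contrast of these correlations between arms follows. The same paragraph does spell out a comparison of intervention with control sites for intention to use and for satisfaction. A site-level agreement measure also appears there ("calculate the proportion that are in agreement with local public baseline priorities (ranks 1 to 5"), but only for descriptive reporting.

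On clustering the section says: "We will check the data to assess the level of clusterisation within study sites and use appropriate cluster-level analysis", to be used only where that check shows a need, with multilevel modelling as an example. The 0.05 threshold applies to every test ("two-tailed test) for all tests").

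**The concern.** Two things are badly fixed. First, the analysis labelled primary does not carry the arm comparison that defines the primary outcome. A correlation between professionals and public describes agreement inside whatever group it is computed for. Its p-value concerns a correlation of zero in that group and says nothing about the effect of randomisation.

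Second, sites are randomised, but whether the analysis respects sites depends on the data. With so few sites, a check that finds no clustering is weak evidence that none exists. An analysis that then ignores sites treats the wrong units as independent. What is at stake is the validity of the p-value on the trial's only primary hypothesis.

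**Working it through.** **1. Unit of the correlation.** The section Identification of quality indicators says: "The final menu of indicators is composed of 37 menu items (Table 1"). The correlated quantities are proportions or ranks per indicator, so the natural n is 37. This is an inference; the article does not state the unit.

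**2. Allocation.** No ratio is stated, so I take it from the recruitment targets in Table 3 and the Sample size section.
- Public representatives: 15 × 6 = 90, as stated.
- Step 3 decision makers: 10 × 6 = 60, as stated.
- Step 2 professionals: 9 × 6 = 54 does not give the stated 72. With k intervention sites at 9, and control groups filled to 15, 9k + 15(6 − k) = 72 gives k = 3.

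A 3 v 3 split is therefore inferred. The article gives no power figure to reproduce.

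**3. What the correlation's p-value tests.** With n = 37, t(0.975, 35) = 2.030, so the critical |r| = 2.030/√(35 + 2.030²) = 0.325. By Fisher z with SE 1/√34, and with no intervention effect, the chance that one group's correlation is significant is:

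| Assumed true correlation | P(significant) |
|---|---|
| 0.2 | 0.22 |
| 0.3 | 0.44 |
| 0.4 | 0.69 |
| 0.5 | 0.89 |

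Significance here reflects existing agreement, not involvement.

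**4. Cost of ignoring sites.** I simulated 2,000 trials per setting with no intervention effect. Each site had 15 public members and 10 professionals, each picking 5 of 37. The underlying professional-public correlation averaged 0.4, and its Fisher z varied between sites with an assumed SD. Two tests of the arm difference were compared: Fisher z on the arm-pooled correlations, (z₁ − z₂)/√(2/34), and a t-test on the six site-level Fisher z values.

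| Assumed between-site SD of Fisher z | Type I error, pooled, n = 37 per arm | Type I error, six-site t-test |
|---|---|---|
| 0 | 0.02 | 0.05 |
| 0.2 | 0.05 | 0.05 |
| 0.4 | 0.13 | 0.05 |
| 0.6 | 0.23 | 0.06 |

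**5. Can six sites inform the check?** With 3 v 3, the between-site variance within arms has 4 degrees of freedom. Its 95% interval on the SD scale runs from √(4/11.14) = 0.60 to √(4/0.484) = 2.87 times the estimate. Such an estimate cannot separate the harmless rows of the table from the harmful ones.

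**6. What a site-level contrast can deliver (3 v 3).**
- Difference needed for p < 0.05: t(0.975, 4) × √(2/3) = 2.776 × 0.816 = 2.27 between-site SDs.
- Power by noncentral t: 0.16 at 1 SD, 0.46 at 2 SD, 0.78 at 3 SD and 0.80 at 3.07 SD.
- Exact permutation: C(6,3) = 20 allocations, so the smallest two-sided p is 2/20 = 0.10.

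**The case against.** The strongest reply is that the article must be read as a whole. The arm comparison is stated in the outcome definition, and the Statistical analysis section only explains how agreement is measured. A condensed article may leave the exact test to a fuller plan. The section also warns about clustering, and multilevel modelling is only an example, so a comparison of site summaries is permitted. Low power is already disclosed. Much of this stands, and it rules out several stronger readings.

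- A reader might infer that the plan has no arm comparison or site-based analysis, so that none of its p-values could test the hypothesis. The comparison is clearly intended, and a site-based analysis is allowed. Individual agreement scores could also be modelled with site effects. The limitation applies to the correlation's own p-value.
- A reader might expect the trial to conclude from a significant correlation in one arm and not in the other. Nothing in the article plans that.
- A reader might hold that a test on 37 indicators always rejects too often. It does not. The table shows 2% to 5% at between-site SDs of 0 to 0.2, and a separate simulation over other assumed preference spreads gave 1% to 6%. Inflation needs larger between-site variation, and the article gives no figure for it.
- A reader might conclude that public members' later views are the end-of-trial comparator, so that their movement towards professionals would count as success. The wording is ambiguous. The time points can simply say when the correlation is calculated, and the section Quality-indicator prioritisation assigns postdeliberation responses to process evaluation.

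Two things are not answered: the analysis labelled primary does not match the outcome as defined, and the clustering rule is stated and is conditional. These are choices the article makes, not details it leaves out.

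**Conclusion.** The point holds as a mismatch and a badly fixed rule. The primary hypothesis and outcome compare arms. The stated primary analysis is a within-group correlation whose p-value does not test that comparison. Protection against clustering depends on a check that six sites cannot support. If sites are ignored, type I error could lie anywhere from about 2% to 23% over the assumed range of between-site SDs, against 5% to 6% for a site-level t-test.

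The conclusion assumes that the indicator is the unit of the correlation and that the split is 3 v 3, both inferred. The error rates also depend on the simulation model. The simulation treats sites as independent. The section on the Step 3 meeting describes one joint meeting for all intervention sites and another for all control sites, so end-of-trial values within an arm may be dependent, and a site-level test does not remove that.

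**What to change.** In the Statistical analysis section:

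- Compute agreement within each site between the clinicians' and managers' end-of-trial priorities (questionnaire Q8 in Table 4) and that site's Step 1 public list (questionnaire Q2). Exclude public members' later responses, which exist only in intervention sites.
- Name one primary contrast, not conditional on any check: the difference between arms in mean site-level agreement, for example the Fisher z of each site's correlation. Give a t-based 95% CI, with 4 degrees of freedom if the split is 3 v 3, and state the split.
- Show baseline professional agreement (questionnaire Q5) descriptively only. It should not enter as an individual change score, because Step 2 and Step 3 professionals only partly overlap.
- Report arm-level correlations descriptively.
- State the limits: about 2.27 between-site SDs for p < 0.05, about 3.1 for 80% power, a permutation p that cannot fall below 0.10 with 3 v 3, and possible dependence within arms from the joint Step 3 meetings.

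This changes wording only, since the data needed are already planned. The price is less favourable p-values, with the estimate and its interval as the headline.

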## Methodology

### Project overview and design

We will conduct a cluster randomised controlled trial that will assess the impact of public involvement on quality-indicator choice and intended use (Figure 1). A cluster design is warranted because of our interest in group decision making. In preparation for the trial, we have developed a 'menu' of validated quality indicators based on a systematic review of the literature and expert consultation. We also pilot tested our intervention and instruments. Participants (public representatives, clinicians, and managers) will be recruited from six participating sites, which will be randomised in intervention (quality-indicator prioritisation with public involvement) and control sites (without public involvement).

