### Description of the intervention

The intervention is composed of three one-day meetings (step 1, step 2, and step 3) that aim at prioritizing local quality indicators. The Regional Health Authority expects that the selected indicators will be used to support continuous quality improvement of chronic disease prevention and management (rather than for external control or benchmarking), and each local health authority will be allowed to select its own indicators. The selected indicators will be integrated in the regional accountability contracts signed with each local health authority. Table 3 summarises the topics addressed in each intervention meeting, and their content is described in detail below.

**Table 3 T3:** Intervention meetings' content

Meetings	Participants	Content
**Step 1: Public representatives' training and recommendations**	Public representatives (Target: 15/site)	• Participants' discussion on positive and negative experience in relation to quality of care • Information on chronic disease and local prevention and management services • Explanation of the indicator menu and data collection on baseline public recommendations

**Step 2: Group recommendation**	Clinicians and managers (Target: 9/site) and public representatives (Target: 6/site)	• Individual baseline prioritisation • Deliberation on indicator choice ○ Block 1 (Structure: access and integration) ○ Block 2 (Process: technical quality and interpersonal care) ○ Block 3 (Outcome indicators) • Final group recommendation and individual recommendations

**Step 3: Decision makers' meeting**	Clinicians and managers (Target: 10/site) and public representatives (Target: 2/site)	• Expectations from the Regional Health Authority on quality-indicator choice and use • Presentation of recommendations issued in step 1 and step 2 meetings • Deliberation on indicator choice and implementation • CEOs summarise decisions and foresee actions for each local health authority

CEO = chief executive officer.

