### Sample size

Our sample size calculation is based on pragmatic considerations and takes into consideration the maximum number of available sites/clusters in the region (n = 6 sites) and the maximum number of recommended participants in small-group deliberation meetings (n = 15 participants per meeting). We aim to recruit a total of n = 90 public representatives, n = 72 clinicians and managers for the step 2 meeting, and n = 60 senior managers and professional council representatives for the step 3 meeting. We will allow for overlap between clinicians and managers participating in step 2 and step 3 meetings.

Abelson and colleagues note that small sample sizes are hard to overcome in studies of public participation in healthcare as 'deliberation decision-making dictates small groups' [13]. We expect that the power of our study will be further decreased by the cluster nature of the trial, although we are currently unable to estimate the magnitude of this effect due to the absence of prior trials of public involvement in quality-indicator prioritisation and unknown intra-cluster coefficients for our outcome of interest [93].

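### Adjustment for clustering depends on an unspecified look at data from six sites, which can push the participant-level arm comparisons to roughly twice the stated 5% error or more

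*Protocol article*

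**What the plan says.** All references are to the protocol article. Under Project overview and design, participants "will be recruited from six participating sites, which will be randomised in intervention" and control sites, so the site is the unit of randomisation. Sample size gives "the maximum number of available sites/clusters in the region (n = 6 sites") as the ceiling.

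Statistical analysis recognises the issue: "Cluster randomisation leads to a reduction of effective sample size and can give spurious statistical results if it is not accounted for properly". The next sentence sets the rule: "We will check the data to assess the level of clusterisation within study sites and use appropriate cluster-level analysis", with the example and condition "multilevel modelling) if necessary". No test, threshold or ICC cut-off is attached to that condition. Significance is set at p "< 0.05 (two-tailed test) for all tests". The same section plans to compare intention to use and satisfaction between intervention and control sites. Sample size adds that there are "unknown intra-cluster coefficients for our outcome of interest".

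No other section makes the adjustment unconditional.

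**The concern.** Once sites are randomised, the variation between sites is the error against which an arm difference must be judged, whatever ICC happens to be observed. A rule that drops this error term when the data do not appear to need it relies on the data to show that clustering is absent. With three sites per arm, only 4 df are available for that judgement.

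Clustering is plausible for the two outcomes compared at participant level. Intention to use is recorded after each territory's decision makers have agreed on their indicators, so colleagues rate the same chosen set. Satisfaction is a rating of meetings that participants shared. The Sample size section itself expects clustering to reduce power. If the adjustment is skipped when clustering is present, standard errors are too small, and a chance difference between sites can be reported as an effect of public involvement.

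**Working it through.** **Inputs from the article.** Two-sided alpha 0.05; six sites. Table 3 gives the step 3 participants as "Clinicians and managers (Target: 10/site) and public representatives (Target: 2/site"). The maximum per meeting is 15.

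**The article's own figures.** It states no power and no ICC, only recruitment targets. 15 × 6 = 90 public representatives and 10 × 6 = 60 decision makers reproduce. For the 72 step 2 professionals, 9 × 6 = 54 does not fit, but 3 × 9 + 3 × 15 = 72 does (control meetings filled to 15). This supports a 3:3 split, which the article does not state.

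**Assumptions.** 3 v 3 sites; equal site sizes of m = 10, 12 or 15; normal outcome; ICC from 0 to 0.5; trigger = F-test of sites within arm at 5%. At m = 10 this test has 6 − 2 = 4 and 60 − 6 = 54 df.

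**Step 1: never adjusting.** The design effect is DE = 1 + (m − 1) × ICC, and the error is about 2[1 − Φ(1.96/√DE)]. At m = 10:
- ICC 0.05: DE = 1 + 9 × 0.05 = 1.45; error 10.4%.
- ICC 0.10: DE = 1.90; error 15.5%.
- ICC 0.20: DE = 2.80; error 24.1%.

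**Step 2: the conditional rule.** Simulation of 40,000 trials per setting with no true effect (Monte Carlo standard error at 10% is √(0.1 × 0.9/40,000) = 0.15 percentage points). If the F-test is not significant, an unadjusted t-test is used. If it is significant, either a t-test on site means (4 df) or a multilevel model with a normal (Wald z) reference is used. Ranges run over m = 10, 12 and 15; all entries are percentages.

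| ICC | Clustering detected | Never adjust | Check, then 4-df t | Check, then multilevel z | Always 4-df t |
|---|---|---|---|---|---|
| 0 | 5.0–5.3 | 4.9–5.0 | 4.6–4.8 | 4.6–4.8 | 4.9–5.1 |
| 0.01 | 6.9–8.3 | 6.0–6.5 | 5.7–6.0 | 5.7–6.0 | 4.8–5.1 |
| 0.02 | 9.0–11.9 | 7.0–8.3 | 6.3–7.4 | 6.4–7.4 | 4.9–5.1 |
| 0.05 | 17.1–24.6 | 10.3–13.2 | 8.7–10.0 | 8.9–10.2 | 4.8–5.0 |
| 0.10 | 32.0–45.3 | 15.6–20.7 | 10.9–11.7 | 11.4–12.7 | 4.8–4.9 |
| 0.20 | 57.7–71.8 | 24.9–32.6 | 10.6–11.5 | 13.4–13.8 | 4.9–5.1 |
| 0.30 | 75.1–85.5 | 32.9–41.0 | 8.1–10.0 | 13.1–13.5 | 4.7–5.0 |
| 0.50 | 91.9–96.1 | 44.0–52.6 | 5.8–7.0 | 12.4–12.8 | 5.0–5.2 |

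**Step 3: sensitivity to the trigger.** With the 4-df test as the follow-up, a trigger of p < 0.20 gives 3.9–7.5% over the same ICCs, and a trigger of any positive ICC estimate gives 3.0–5.3%.

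**Step 4: unconditional multilevel modelling.** If always fitted but judged by a plain Wald z, the error is 7.1–12.1% at ICC 0.05 to 0.5. The limit is P(|t on 4 df| > 1.96) = 12.2%. Removing the condition is therefore not enough on its own; the reference distribution matters too.

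**The case against.** A reader might infer that the comparisons will run well above 5%. The article does not support that. The ICC is unknown and the trigger is unstated: at ICC 0.01 to 0.02 the inflation is small, and a liberal trigger with a 4-df test roughly holds the level. The F-test is an assumption made here; assessing the level of clustering could equally mean estimating an ICC. Nor is it right that the check usually misses clustering: at ICC 0.20 it succeeds in more than half of trials.

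A reader might also carry these figures over to the primary outcome. For that outcome the article names a correlation between professional and public priorities and no between-arm test, and site-level indicator choices are reported descriptively. The figures fit only the participant-level comparisons.

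It would also be too strong to fault multilevel modelling as such. It is offered as an example, no reference distribution is stated, and the df method is commonly left to an analysis plan. And the authors do not overlook clustering: they warn about it, expect lost power, and list the small effective sample size as a limitation in the Discussion.

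These points narrow the size and the scope. They do not defend the rule. The article states a conditional rule and does not merely leave a detail open, and whether 5% holds then turns on a choice made after seeing the data.

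**Conclusion.** The point holds in limited form. Making the cluster adjustment conditional, with no criterion, is unsound when sites are randomised and there are only six. For intention to use and satisfaction, the error can reach roughly 9–14% at ICC 0.05 to 0.30 (8.1% in the most favourable setting in that range). This rests on a 3:3 split, 10 to 15 participants per site, a normal outcome and a 5% F-test trigger. With a small ICC or a liberal trigger the excess is slight or absent. No figure can be given for the primary correlation.

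One limit applies to the remedy as well. The section on the step 3 meeting describes one joint semiregional meeting for all intervention sites and another for all control sites. The 5% shown for the site-level test assumes that sites within an arm are independent. Any effect of the meeting itself on intention to use or step 3 satisfaction coincides with arm, and neither site summaries nor a site random effect can remove it.

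**What to change.** In Statistical analysis, delete both the data check and the closing condition. State that every between-arm test accounts for site whatever ICC is observed, by one of two methods named in advance:
- a two-sample t-test on six site summaries, with 4 df; or
- a mixed model with a site random effect and Kenward-Roger or Satterthwaite df.

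Report the ICC descriptively. An exact re-randomisation test is not a substitute at this level: a 3:3 split has 20 allocations, so the smallest two-sided p is 2/20 = 0.10.

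Add as a limitation that step 3 is one joint meeting per arm, so that a meeting effect cannot be separated from the effect of public involvement.

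The change is one of wording and needs no new data. It costs wider confidence intervals and less power, which fits the article's own statement that the effective sample size is small.
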